PFP is simple and effective. A village agrees to join PFP and develops a village PFP association. An association in the villages supports the families in managing the pigs, from building enclosures, to vet services, to education on food and health of pigs, and how to bring others into the association. The village association agrees to meet monthly to discuss challenges and solutions as well as successes for the PFP project. The village association meetings have also become a source of ongoing strengthening of social capital and social network, where important health and human rights related information is shared. The village PFP association decides what member households in the village receives the female pig and the association delivers the pig to the selected village households with the female head of household the primary target audience. The project also provides adult male pigs to the village association for the initial breeding. Each participating household agrees to repay their “loan” by giving one piglet to the PFP association from the first two litters of piglets. These piglets are then given to other village households in the association, allowing PFP to grow rapidly and serve families in need of resources to sustain and rebuild their lives.

The pigs are providing sources of sustainable, supplemental income, with pigs giving birth frequently – 2 times a year with up to 6-12 piglets at each birth. In July-August, 2009, an initial PFP evaluation was completed with the first 25 village women who received the pig loan. The participants who had a pig give birth reported using funds from selling pigs ($20-$40 each) to pay for their children’s school fees, clothing, and medicine, to build a house, and/or to invest in other small businesses. This amount of household income is significant in this area, as some households report living on $1-$3 a day.^55^

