**APPROACH**

The study was developed by our collaborative microfinance-academic team that has been working together for the past 3 years to improve the health and well-being of participants and their families. Our demonstrated success in partnership, complementary qualifications of team members and preliminary findings has convinced the team to propose a five-year experimental trial using a mixed-methods (quantitative and qualitative) approach to successfully achieve the study aims. The following section describes the teams’ specific aims and approach in detail.

Design Overview for Specific Aims 1 & 2

Ten villages in the Walungu Territory in South Kivu, DRC will be selected through a village assessment. A total of 10 villages will be selected for participation. Sixty-six households in each village will then be randomized to intervention (receive 1^st^ loan pig) and control (receive 2^nd^ loan pig) groups. Outcomes will be measured at the individual and household levels in both intervention and control villages. Measurement of outcomes in each village will use self-report by village household members. An eligible household has at least one individual (16 years or older). The study will be conducted over five years. Intervention and control group outcome data will be collected at baseline and, 6, 12 and 18-months post-baseline assessment.

Study Setting:

The study will take place in the tribal chiefdom of Ngweshe, which is located in the Walungu territory, South Kivu, DRC. The Chiefdom is 40 km south of Bukavu, the capital city of South Kivu, and has an estimate population of 700,000 residents and was chosen by the research team and collaborating Congolese partners for several important reasons: 1) this rural area has suffered significantly from the war over the past 15 years because of its proximity to mineral resources (e.g. gold and coltan) and isolation related to limited infrastructure; 2) very limited humanitarian and/or development resources, including microfinance have reached the Chiefdom; and 3) the team has a strong history of collaboration (over 3 years) with Congolese physicians, nurses, agriculture technicians, community health workers, religious leaders and village leaders working in the Walungu Territory to better understand the needs of the villagers.

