The number of villages included in the study was determined by the operational feasibility of delivering the intervention over a wide geographical area, the time required for recruitment and follow-up, the need to enroll all eligible households in a village before expanding, and ethical concerns about withholding participation from control villages. A planned 10 villages in the Chiefdom will be selected for the study. Randomization of 66 households that have expressed interest in the study will be done during a research team meeting. One household name will be drawn blindly and assigned to the intervention group and then the next assigned to control and so on until complete for each village. Before the study, no village will have access to microfinance or the PFP program. Participating village populations have 75-100 households, with typically over 50% of village population being female, because of the loss of boys and men to violence or leaving the village to find work to help support the family.

Phase One: Description of Village Assessment and Informational Meetings

In Phase One (Year 1), we will complete the following study related activities: 1) village assessment: the socioeconomic characteristics (health clinics, schools, markets, economic activities, etc) and the number of households in the village and the number of households with women ages 16 years or older in 10 potential study villages in the Chiefdom will be assessed through field reconnaissance surveys and interviews with village members; 2) the study team will then meet with village leaders (traditional and governmental) in the selected 10 villages in the Chiefdom to invite them to participate in the study. If a village decides not to participate after the initial meeting, the team will meet to select another village to invite based on the field assessments. The invitation meeting will be held in the villages with leaders to discuss the study goals, explain the study design, including an explanation of randomization and intervention and delayed control groups. The team and village leaders will organize the informational meeting and invite all village households to attend and participate in the discussion; and the team will recruit and train (study protocols, human subjects protection) one (female or male) research assistant to work with 2 village each.

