*Informational Sessions:* In year one, the informational sessions for households in participating villages will include: 1) introduction to study team members and 2) introduction to the animal husbandry-based microfinance program, Pigs for Peace (PFP), under the direction and management of PAIDEK. The informational session will allow for village education, dialogue and questions related to microfinance and specifically, PFP. The outcome of the informational session will be the establishment of the PFP Village Association and leadership. Village Association membership is opened to villagers 25 years of age and older, regardless of gender. Membership in the Pigs for Peace Association is not limited to individuals who have reported or been identified as survivors trauma and violence for two critical reasons: 1) since the stigma and fear of rejection prevent many survivors of trauma and violence from reporting their cases or self-identifying as survivors, we do not want to limit access to services to women/men who have disclosed the violence; 2) rural women and men who are willing to invest time and resources in Pigs for Peace will be placed on the participation list for the loan of a pig. Further, engagement of village men in the associations will encourage their participation in the success of the project and their input on strategies to reduce stigma and isolation. Pigs for Peace village associations leadership committees, made up of men and women, will decide on the loan recipients. PAIDEK will work closely with the village associations to set up bylaws, membership rules, monthly meetings, loans and repayment, and monitor and collect data on outcomes.

*Village Household Recruitment:* In participating villages, the village leaders will work closely with the village based RAs, study coordinator and research team members to select household that meet the eligibility criteria: household with at least one member 16 years or older who is head of household, interest in animal husbandry microfinance, low-income, widow, survivor of sexual violence, children in the home. We estimate 66 households in each participating village will be eligible and consent to participate, for a total of 330 intervention households and 330 control households.

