*Baseline Data Collection:* The study coordinator and village based RAs will visit the eligible households, invite them to participate and inform them of all study related activities. Participants in PFP are not required to participate in the study. If a PFP participant decides to not participate in the study, they will not be removed from the PFP project. Verbal informed consent will be obtained from each household participant prior to collecting baseline interviews. The interviews will be completed in a private setting, perhaps outside under a tree or in a quiet village location. The village based RA will complete the interview using a tablet computer that is pre-programmed with the questionnaire.. We estimate that each study interview will take one hour each. In our previous interviews, one hour was considered reasonable by the participants and did not cause undue burden.

*Study Interview Instrument:* The majority of the instruments have been used in prior work with internally displaced persons (IDPs) and refugees impacted by conflict. The measures have been used with diverse cultural groups in clinical and community settings. The measure includes demographics, quality of life, mental health, functioning, exposure to trauma and violence, family and community relationships, stigma and community support/reintegration.

Intervention Households

Within two weeks of the baseline individual and household member interviews being completed, the intervention household will be provided with the loan, one female pig. The loan recipient will be supported by the PFP village association to breed the pig, manage the health and care of the pig. The support comes through monthly association meetings as well as the study project coordinator providing regular home visits to help problem solve and assess success and challenges. The study village based RAs will complete follow-up face-to-face interviews that consist of the same measures as at baseline at 6,12 and 18-month post-baseline interviews. Eighteen months of follow-up was deemed necessary to provide time for the loan “pig” to successfully breed and have at least one litter. All village based data collection will be monitored and supervised monthly by the PI, co-investigators and coordinator. The team will meet monthly via Skype or, teleconference to discuss on going activities, challenges and successes. This communication strategy has been successfully implemented in previous studies.

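### The protocol gives the choice of first-loan recipients both to a random draw and to village committees, and does not fix the order of draw, consent and baseline

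*Protocol*

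**What the plan says.** **Who receives the first pig.** The Design Overview for Specific Aims 1 & 2 makes the order of the loan the randomised treatment: "Sixty-six households in each village will then be randomized to intervention (receive 1^st^ loan pig) and control (receive 2^nd^ loan pig) groups". Study Setting gives the mechanism: "One household name will be drawn blindly and assigned to the intervention group and then the next assigned to control". This is done at a meeting of the research team.

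Informational Sessions, under Phase One, gives the decision to another body: "Pigs for Peace village associations leadership committees, made up of men and women, will decide on the loan recipients". The background description of the programme agrees with that: "The village PFP association decides what member households in the village receives the female pig".

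**Draw, consent and baseline.** Study Setting defines who enters the draw by interest: "Randomization of 66 households that have expressed interest in the study will be done during a research team meeting". Baseline Data Collection then describes the invitation, "The study coordinator and village based RAs will visit the eligible households, invite them to participate and inform them of all study related activities", and the consent, "Verbal informed consent will be obtained from each household participant prior to collecting baseline interviews". It adds: "If a PFP participant decides to not participate in the study, they will not be removed from the PFP project". Under Intervention Households, the pig follows within two weeks of the baseline interviews. No section says whether the draw comes before or after consent and baseline, or from whom its result is withheld.

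**The concern.** Receiving the first pig is the treatment assignment, so the protocol gives one decision to two bodies. A field team following the draw runs a randomised trial. A team following Informational Sessions lets committees choose the recipients. If committees replace the draw, the arms may differ in prognosis from the start, because a committee may favour households that are needier, more capable or better connected. If committees only exchange some households after the draw, an intention-to-treat comparison by drawn group stays valid but its effect is diluted.

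The open sequence is a second and lesser weakness. Outcomes are self-reported and assignment cannot be hidden once pigs are delivered, so baseline is the only interview that can be protected from knowledge of the arm. If households or interviewers knew the assignment first, agreement to take part and the baseline answers could both depend on it.

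**Working it through.** **1. The plan's own counts.** 10 villages × 66 households = 660. Alternating 1:1 gives 330 per arm, as stated under Village Household Recruitment.

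**2. How much of a village the committees' decision could touch.** Study Setting gives 75–100 households per village, of which 66 are in the study. The share is 66/100 = 66% to 66/75 = 88%. Control households also attend the association meetings (Delayed Control Households). The pool from which a committee would choose is therefore mostly the trial sample.

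**3. The passages side by side.**

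| Question | Design Overview and Study Setting | Informational Sessions and Background |
|---|---|---|
| Who decides? | Blind draw by the research team | Association or its leadership committee |
| What is decided? | First or second loan pig | Who receives the loan pig |
| Limited to certain households or rounds? | The 66 study households | No limit stated |
| Does one rule bind the other? | Not stated | Not stated |

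**4. Consistency of the stated power.** The power statement uses 300 per group and alpha .05. It does not give the SF-8 means, standard deviation or within-person correlation, so power cannot be rebuilt from scratch. As a check, take the power stated at ICC .001, assume a two-sided test and a normal approximation, and rescale by the design effect with m = 600/10 = 60 per village:

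λ₀ = (1.96 + z_power) × √(1 + 59 × .001), and power(ICC) = Φ(λ₀ / √(1 + 59 × ICC) − 1.96).

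| Component | Stated, ICC .001/.005/.010 | Recomputed |
|---|---|---|
| Physical | .94 / .89 / .83 | .940 / .888 / .818 |
| Mental | .91 / .84 / .78 | .910 / .847 / .768 |

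The first value in each row agrees by construction. The others lie within two points, so the stated figures are coherent.

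**5. Dilution from swapping (illustration; rate f assumed).** Suppose a share f of each arm is exchanged and exchanged households have the average effect. The intention-to-treat effect is then (1 − f)δ − fδ = (1 − 2f)δ, and

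power = Φ((1.96 + z_stated) × (1 − 2f) − 1.96).

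Example, physical component, ICC .001, f = 10%: 1.96 + 1.555 = 3.515; × 0.8 = 2.812; − 1.96 = 0.852; Φ = .80.

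| f in each arm | Effect retained | Physical, ICC .001/.005/.010 | Mental, ICC .001/.005/.010 |
|---|---|---|---|
| 0 (stated) | 100% | .94 / .89 / .83 | .91 / .84 / .78 |
| 5% | 90% | .886 / .818 / .746 | .844 / .758 / .691 |
| 10% | 80% | .803 / .722 / .645 | .752 / .657 / .589 |
| 20% | 60% | .559 / .481 / .416 | .508 / .426 / .374 |

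**6. Sequence.** Defining the pool by interest, with invitation and consent at the household visit, fits a draw before consent. The estimate of 66 households per village that qualify and consent, the same 66 that are randomised, fits a draw among consenters. The text supports both and settles neither.

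**The case against.** The best defence is that the committee sentence was never meant to govern the first round. It stands in a paragraph on association membership, which is open to villagers beyond the study households, and repaid piglets are later passed to other association members. The study-specific text is unconditional: the first pig follows randomisation, and the intervention household receives it after baseline. The Background section describes an existing programme, not a trial procedure. This reading is plausible, but it is not written anywhere. The committee sentence belongs to the Phase One procedures for the trial villages and carries no limit by round or household.

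Three stronger readings are tempting and go too far.

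- **That the draw precedes consent.** A reader might infer this from the pool being defined by interest and from the order of the sections. Study Setting is an overview and not a chronology, and the 66 expected to consent fit a draw among consenters.
- **That a household declining the study keeps a first-round pig.** The text says only that it is not removed from the programme. Consent precedes baseline and the pig follows baseline, so whether a decliner would get a first-round pig is unstated.
- **That a modest imbalance inflates the false-positive rate to a known figure.** A 0.1 SD bias at 300 per arm gives a shift of 0.1 × √(300/2) = 1.22 and a two-sided rejection rate of about 23% in a comparison at one time point. The planned test is group by time, where a stable difference in level does not bias change. Nothing in the protocol supports 0.1 SD.

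**Conclusion.** The conflict over who decides the first loan is real and unreconciled, and it must be fixed because the trial's causal aim depends on random assignment. The pledge to analyse by intention to treat does not help if recipients were chosen instead of drawn.

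The size is conditional. If committees replaced the draw, the comparison would not be randomised, and the documents give no basis for the amount of bias. If they swapped a minority after the draw, the cost is power: at 10% in each arm, about 14 to 19 percentage points for the physical component and 16 to 19 for the mental component across the three ICCs. The swap rates are assumed, and the calculation rests on a two-sided test, a normal approximation and an average effect in swapped households. No stated power figure is shown to be wrong, and override is a risk created by the text, not a procedure that it prescribes.

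On timing, the supportable conclusion is narrower. The order of draw, consent and baseline, and concealment until baseline is complete, are not fixed. This would not carry the same weight alone, but it belongs in the same correction.

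**What to change.** Make two wording changes.

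1. **Informational Sessions:** state that for the 66 study households in each village the random draw alone determines who receives a first-round loan. Committees decide only on loans outside that allocation and on association matters. A short note in the Background section that its description is of the general programme would remove the echo.
2. **Study Setting:** state that the draw, or disclosure of its result to households and interviewers, takes place only after the household has consented and completed its baseline interview.

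The cost is a small scheduling constraint. Holding each village's draw until all 66 households have finished baseline could strain the two-week interval to the loan, since one research assistant covers two villages and each interview takes about an hour. Drawing in advance, keeping the result concealed and releasing it household by household after baseline avoids this and leaves the two-week interval unaffected. Sample size and analysis do not change.

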The US plays a significant role in global health. It is both the largest funder of innovation in global health and the largest donor to care and support programs in sub-Saharan Africa—notably through PEPFAR and responses to humanitarian crisis, such as USAID funded programs in DRC. The effectiveness and sustainability of these efforts are limited by gaps in knowledge of the role of social determinants, such as poverty, social isolation, chronic stress and trauma, and limited access to health care services has on the health of women and families.^9^ To begin to address these gaps, our overall goal is to build the science base for large-scale implementation of economic programs to improve the economic security and health in man-made and natural disaster settings. The objective is to test the effectiveness of an established innovative, village-led microfinance program, Pigs for Peace, on health, household economic stability, and reintegration to family and village. Our preliminary evidence indicates that a village-led animal husbandry microfinance program improves Congolese women’s health and household economic stability, through increased funds to purchase food, housing and medication and to pay school fees for children. Survivors report a reduction in the negative health impacts of chronic stress, stigma and trauma associated with trauma and violence because they are once again productive family and village members. Therefore, a five-year experimental trial will be conducted using mixed-methods to address the following aims:

**1. Determine the effectiveness of a village-led microfinance program on participant health and reintegration in intervention households compared to participants in delayed control households.** Health and reintegration will be measured at baseline and six, twelve, and 18-months post-baseline using self-report in both intervention and control groups. We hypothesize that at six, twelve and 18 months post-baseline participants in intervention households will have improved health and increased reintegration to families in comparison to control households.

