*Process Evaluation*: Along with the individual and household measures collected at baseline and follow-up interview, a process evaluation of the PFP project performance in each intervention village will be completed at the end of 18 months with a sub-sample of association leaders and participants and include: 1) number of participants in village association; 2) number of pigs “loaned”; 3) health of pig and piglets; 4) repayment of loan piglets to association; 5) distribution of loan piglets to other members of association; 6) satisfaction with Pigs for Peace by association members; 7) opportunities to diversify loans, include rabbits and guinea pigs in the project. The findings from the process evaluation will be used to inform future large-scale implementation of the PFP program.

Delayed Control Households

Delayed control household procedures and data collection is consistent with that presented above in the intervention households. Control households will agree to participate in a monthly village association meeting. The control households will be eligible to receive the repayment of the loans from the intervention groups as consistent with the PFP model. The control households will receive their loan pig after the first year of the project.

Data Management and Analysis for Specific Aims 1 & 2

All research team members will successfully complete research training on responsible conduct of research (RCR) using the on-line Collaborative Institutional Training Initiative (CITI) prior to their involvement in the study. All research team members will receive and review documentation on policies and procedures for managing and reporting any emergency situations or adverse events that might arise during the study. An on-line training program for RAs is prohibitive, therefore the PI ([name] is able to speak French) will complete face-to-face training on RCR. The study investigators, who have many years of experience in the field of SGBV and intervention research, will train all village based research staff prior to their involvement in the study. The training will include sensitization to experiences of SGBV, maintaining the confidentiality of all research participants, intervention protocols and fidelity to protocols as well as issues related to informed consent and adverse events. All research staff members will receive a training manual (French and English) as a reference and resource.

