*Sample size calculation:*  We used data from Roberts and colleagues^56^ study of the reliability and validity of the SF-8 with a conflict-affected population in northern Uganda as the basis for our power analyses. We based the power analysis on repeated measures ANOVA, but propose to use multilevel modeling for the analyses that allows all cases with missing data to be included in the analyses. We do not have adequate estimates of the within and between variance to estimate power for the multilevel model directly. However, in general multilevel model approaches are more powerful than repeated measures ANOVA^62^. Since we do not have an estimate of the intraclass correlation (ICC) (individuals nested within villages) we varied the ICC from .001 to .010. For a sample size of 300 per group and assuming no change from baseline to 18 months in the control group and a 10% improvement in the intervention group, an alpha level of .05, the power to detect a significant group by time interaction for the physical health component score of the SF-8 Is .94, .89, and .83 for ICCs of .001, .005, and .010, respectively. Similarly power to detect a significant group by time interaction for the mental health component score of the SF-8 is .91, .84, and .78 for ICCs of .001, .005, and .010, respectively.

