## Importance of knowledge gained and potential benefits of the proposed research to the participants and others

Trauma and violence is a global health issue and is a violation of human rights and has been used as a weapon of war in the DRC. The multiple interrelated and complex social determinants of health, such as poverty, stigma, chronic stress and trauma, and limited access to health care services impacts the health of individuals, their household and village. As a major donor to global health and humanitarian crisis, the US needs improved evidence of sustainable community-led intervention models for improved health outcomes to reduce health disparities in low-income countries. Research findings from the three study aims will inform the science base for large-scale implementation of structural interventions, with the aim to establish a causal relationship between a village-led microfinance intervention and increased health, household economic stability, and reintegration for survivors of trauma and violence. Further, the study will provide the basis for the transferability of the intervention to other settings, including man-made and natural disaster settings.

Table 2: Study Timeline

| **Activity** | **Year 1** | | | | **Year 2** | | | | **Year 3** | | | | **Year 4** | | | | **Year 5** | | | |
| --- | --- | --- | --- | --- | --- | --- | --- | --- | --- | --- | --- | --- | --- | --- | --- | --- | --- | --- | --- | --- |
|  | Q1 | Q2 | Q3 | Q4 | Q1 | Q2 | Q3 | Q4 | Q1 | Q2 | Q3 | Q4 | Q1 | Q2 | Q3 | Q4 | Q1 | Q2 | Q3 | Q4 |
| IRB approval/study set-up/training of RAs/village consent | X | X | X | X |  |  |  |  |  |  |  |  |  |  |  |  |  |  |  |  |
| Recruitment/retention (Household) |  |  |  | X | X |  |  |  |  |  |  |  |  |  |  |  |  |  |  |  |
| PFP Intervention households |  |  |  |  | X | X | X | X | X | X |  |  |  |  |  |  |  |  |  |  |
| Delayed control households (association meetings) |  |  |  |  | X | X | X | X | X | X |  |  |  |  |  |  |  |  |  |  |
| Delayed control households (intervention) |  |  |  |  |  |  |  |  |  |  | X |  |  |  |  |  |  |  |  |  |
| Follow-up contacts (intervention/control) |  |  |  |  |  | X | X | X | X | X | X | X | X | X | X | X |  |  |  |  |
| Retention follow-ups (intervention/control) |  |  |  |  |  | X | X | X | X | X | X | X | X | X | X | X |  |  |  |  |
| Fidelity Monitoring |  |  |  |  |  | X |  | X |  | X |  | X |  | X |  | X |  | X |  |  |

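### The text and Table 2 of the protocol disagree on when control households get their pig; on the natural reading of the text, controls hold pigs before the 18-month interview, against the power assumption

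*Protocol*

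**What the plan says.** **Timing in the text.** The Delayed Control Households section says "The control households will receive their loan pig after the first year of the project". A separate sentence there says "The control households will be eligible to receive the repayment of the loans from the intervention groups" and gives no earliest date. The two sentences need not describe the same animal. In the other arm, within two weeks of the baseline interviews, "the intervention household will be provided with the loan, one female pig" (Intervention Households).

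**Timing in Table 2.** The row beginning "Delayed control households (association meetings" is marked from Year 2 Q1 to Year 3 Q2. The row beginning "Delayed control households (intervention" has a single mark, in Year 3 Q3. Household recruitment is marked in Year 1 Q4 and Year 2 Q1.

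**Use of the 18-month visit.** Aim 1 states "We hypothesize that at six, twelve and 18 months post-baseline participants in intervention households will have improved health", relative to control households, and Aim 2 does the same for economic stability. The Intervention Households section justifies 18 months as the time needed for the pig to breed and have at least one litter. The sample size calculation gives power for the group-by-time interaction "assuming no change from baseline to 18 months in the control group and a 10% improvement in the intervention group". The analysis is an intention-to-treat multilevel model over baseline, 6, 12 and 18 months.

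**Meetings.** "Control households will agree to participate in a monthly village association meeting" (Delayed Control Households).

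**The concern.** The 18-month visit is the one chosen to let the loan pay off, and the power calculation holds the control arm still until then. If control households receive pigs at about 12 months, that assumption fails at the visit where it matters most. The comparison there becomes earlier versus delayed loan rather than pig versus no pig. If controls benefit, the 18-month difference shrinks and the stated power overstates the chance of detecting it. A null result at 18 months could then mean either that the loan does not work or that the controls had begun to catch up. Because the text and the timeline point to different dates, field staff could follow either one.

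**Working it through.** **1. The two schedules.** Number the quarters of Table 2 from 1 to 20.

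- Intervention households: Year 2 Q1 to Year 3 Q2, quarters 5 to 10, six quarters or 18 months.
- Control households, meetings only: the same six quarters.
- Control households, intervention: Year 3 Q3, quarter 11.
- Text, read as one year after the intervention starts: end of quarter 8. Control pigs then arrive two quarters (6 months) earlier than in Table 2, so controls have up to 18 − 12 = 6 months with a pig by the last interview.

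**2. Table 2 taken alone.** Month 18 falls six quarters after baseline. A household with baseline in Year 1 Q4 (quarter 4) reaches it in quarter 10, before control delivery. A household with baseline in Year 2 Q1 (quarter 5) reaches it in quarter 11, the quarter of control delivery. Table 2 does not say which comes first.

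**3. The plan's own power figures.** For 300 per group and ICC .001/.005/.010, the protocol gives .94/.89/.83 (physical) and .91/.84/.78 (mental). The SF-8 standard deviation, baseline mean and repeated-measures correlation are not given, so these cannot be rebuilt independently. Their mutual consistency can be checked. Take 600/10 = 60 participants per village, design effect 1 + 59 × ICC = 1.059/1.295/1.590, two-sided alpha .05 (sidedness is not stated), and power = Φ(d√(n/2) − 1.96) with n = 300/design effect. A standardized effect d of about 0.298 gives .94/.89/.82, and 0.278 gives .91/.85/.77. One effect per scale therefore fits all three figures to within about one point.

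**4. Dilution.** Let f be the share of the planned effect that controls have gained by month 18. In a normal approximation for a single contrast,

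power = Φ[(1.96 + z_p)(1 − f) − 1.96],

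where z_p is the normal quantile of the stated power. The term 1.96 + z_p is 3.515/3.187/2.914 (physical) and 3.301/2.954/2.732 (mental).

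| f | Physical, ICC .001/.005/.010 | Mental, ICC .001/.005/.010 |
|---|---|---|
| 0 | .940/.890/.830 | .910/.840/.780 |
| 0.10 | .886/.818/.746 | .844/.758/.691 |
| 0.20 | .803/.722/.645 | .752/.657/.589 |
| 1/3 | .649/.565/.493 | .595/.504/.445 |

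The last row is linear accrual, 6 of 18 months. Example: 3.515 × 2/3 − 1.96 = 0.383, and Φ(0.383) = .649. Restoring the stated power at f = 1/3 would take 1/(2/3)² = 2.25 times the sample.

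**5. All four visits together.** For a linear group-by-time slope, the visits at 0, 6, 12 and 18 months have weights −9, −3, 3 and 9. As planned, the group differences are 0, 1/3, 2/3 and 1 of the effect, with weighted sum −1 + 2 + 9 = 10. With f = 1/3 at month 18 they are 0, 1/3, 2/3 and 2/3, with sum −1 + 2 + 6 = 7. The slope keeps 70% of its size, and power becomes .69/.61/.53 (physical) and .64/.54/.48 (mental).

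**The case against.** **The wording is loose enough to fit Table 2.** Taken only as a lower bound, a date after the first year is satisfied by Year 3 Q3. If the project's first year is study Year 1, which is set-up, the sentence would allow control pigs as early as the intervention pigs. This stands as a reason not to assert that controls will cross over at month 12. It does not remove the problem, because none of these readings guarantees that controls stay without a pig until month 18.

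**The dilution may be small.** The protocol expects that up to 18 months may be needed for a litter, and the gains it reports came from selling pigs after a birth. Six months with a pig might yield little. The background also describes two births a year, so the documents do not settle f. A reader might infer larger losses, for example .42 and .38 at ICC .001 if controls gained half the effect. That goes beyond linear accrual (1/3), and nothing in the documents supports it.

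**The comparison is still valid for what was randomized.** The Aims name delayed control households, and the Design Overview defines the arms as receiving the first or the second loan pig. This stands: intention-to-treat is sound for earlier versus delayed loan. The dilution is relative to a comparator with no pig, which is what the power assumption describes.

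**The meetings are planned for both arms.** This stands too. Attendance by controls is stated and scheduled, so it is neither contamination nor a contradiction. It bears only on how the conclusion is worded.

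**Conclusion.** The point holds in conditional form. The text and Table 2 are not reconciled on when controls receive pigs, and repayment piglets have no earliest date. If the text means about 12 months after the intervention starts, the assumption of an unchanged control arm to 18 months does not fit the planned schedule. Power at that visit then depends on an unknown f. It is unchanged at f = 0 and falls to between .49 and .65 (physical) and .44 and .60 (mental) at f = 1/3, across the stated ICCs. Even under Table 2, households with baseline in Year 2 Q1 reach month 18 in the quarter of control delivery. These figures assume a two-sided test, the stated powers as the starting point, and a benefit to controls; without that benefit there is no dilution.

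A reader might infer that the trial's main contrast is already contaminated, or that Aims 1 and 2 cannot be answered. The documents do not support either. Crossover before month 18 depends on which schedule governs. No single primary visit is named. The hypotheses also cover 6 and 12 months, and a pig given after month 12 leaves those comparisons unaffected.

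**What to change.** 1. Reconcile the Delayed Control Households section with Table 2. State when control loan pigs and repayment piglets may be delivered relative to each household's own 18-month interview. Which schedule to adopt is for the investigators.
2. Record the date on which each control household first receives any pig, whether a loan pig or a repayment piglet.
3. Fix in advance, from the reconciled schedule, whether the 18-month comparison is pig versus no pig or earlier versus delayed loan. It should not depend on events during the trial, or one early piglet could change the comparison.
4. Restate power for that comparison, with a range of f if controls can hold pigs before month 18.
5. Since both arms attend association meetings from the start, word the conclusion as the effect of the earlier pig loan among association members.

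The cost is protocol wording, one recorded date per control household (330 planned), and possibly a lower stated power.
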